# *Randomization should be done only after all inclusion and exclusion criteria have been verified*.

### Outcomes

#### Primary Endpoints

Primary endpoints are safety and tolerability. The treatment with fasudil is considered safe for an individual patient if no drug-related serious adverse events (SAE) is recorded through to visit V23. The treatment with fasudil is considered tolerable if participants do not discontinue treatment due to suspected drug-related adverse events (AE). The proportions of patients for whom the treatment is tolerable/safe are derived for each treatment group.

#### Secondary Outcomes

Secondary endpoints are the survival time and the change of ALSFRS-R, ALSAQ-5, ECAS, MUNIX (18), and SVC from baseline to visits V20, V22 and V23. Secondary safety endpoint is safety until V20.

### Biosample Collection Plan

As part of the therapeutic trial we will collect biosamples which will be used for the analysis of pharmacodynamics, disease progression, genotyping and potentially for future studies. EDTA-blood, serum, plasma, urine, and saliva will be collected from all individuals at specified time points. At V20 (or exceptionally on V19 or V18), a CSF sample and a blood plasma sample will be collected to determine the peak concentration of fasudil and hydroxyfasudil as well as ROCK activity (Table 3). Individual alterations of the biosample collection and analysis plan will not be classified as violations of the general study protocol. All biomaterial samples will be stored at the Biobank of the University Medical Center of Göttingen, except for samples that will be analyzed immediately.

**Table 3 T3:** Biosample collection plan.

**Action visit**	**V0 screening**	**V1 BL**	**V2**	**V3**	**V4**	**V5**	**V6**	**V7**	**V8**	**V9**	**V10**	**V11**	**V12**	**V13**	**V14**	**V15**	**V16**	**V17**	**V18**	**V19**	**V20**	**V21**	**V22**	**V23**
Day (d)		1	2	3	4	5	8	9	10	11	12	15	16	17	18	19	22	23	24	25	26	45	90	180
Permitted delta in days (±) to d1	−42		0	0	+3	+3	+4	+4	+4	+4	+4	+4	+4	+4	+4	+4	+4	+4	+4	+4	+4	±3	±4	±5
		Treatment must be completed within 30 days, with a max. of 3 consecutive non-treatment days																						
Treatment IV 2 times daily		x	x	x	x	x	x	x	x	x	x	x	x	x	x	x	x	x	x	x	x			
Biosample collection																								
EDTA-Blood (Genotyping)		X																						
CSF (e.g., Fasudil concentration, NfL)																			(X°)	(X°)	X°			
Plasma (e.g., Fasudil concentration and ROCK-activity)^***^	X	X																	(X°)	(X°)	X°			X
Serum (e.g., NfL, urate)		X																			X			X
Urine (e.g., soluble p75ECR)		X																			X			X
Saliva (e.g., Chromogranin A)		X																			X			X

*X° CSF (and concomitant plasma) analysis will be performed once 60 min after the end of trial drug infusion in the morning, regularly on V20 (exceptionally on V18 or V19). IV-Treatment must have taken place at least on the 2 days preceding CSF/plasma analysis*.

*** *If not routine please perform only after informed consent. All biomaterials must be taken directly after administration of the trial drug in the morning except CSF (see above, X°)*.

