### Drug Procurement and Intervention

Fasudil hydrochloride hydrate will be delivered as medicinal product to the Pharmacy at University of Leipzig Medical Center, Germany, and the trial medication as well as the according placebo will be produced, packaged, stored, blinded, labeled, and shipped to the trial sites in accordance with the regulations of the participating country and good manufacturing practice (GMP) (Annex 13 of the EU Guideline for GMP).

Trial medication will be supplied as fasudil hydrochloride hydrate solution 30 mg for IV application (2 × 1 ml of 15 mg/ml fasudil hydrochloride hydrate), or fasudil hydrochloride hydrate solution 15 mg for IV application (1 ml of 15 mg/ml fasudil hydrochloride hydrate and 1 ml NaCl 0.9%). The appropriate Placebo to fasudil hydrochloride solution will be supplied as 2 × 1 ml NaCl 0.9%. Placebo solution is identical in appearance to the study medication (clear, colorless fluid), but does not contain the active ingredient.

The trial drug or placebo has to be diluted in 100 ml NaCl 0.9% prior to administration and is administered two times daily IV as infusion over 45 min using a CE-certified infusion pump. The second application starts 7 ± 1 h after the start of the first application.

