### Study Procedures

The trial is structured into 24 visits (V0–V23). V0 is the screening visit and may take place up to 42 days before the first treatment. Treatments are then performed twice daily from V1 to V20 on work days, excluding week-ends and holidays. Subsequently, trial participants are seen at three follow-up visits, V21, V22, and V23, at 45, 90, and 180 days after baseline, respectively. The detailed trial plan is shown in Table 2.

**Table 2 T2:** Trial visits schedule.

**Action visit**	**V0 screening**	**V1 BL**	**V2**	**V3**	**V4**	**V5**	**V6**	**V7**	**V8**	**V9**	**V10**	**V11**	**V12**	**V13**	**V14**	**V15**	**V16**	**V17**	**V18**	**V19**	**V20**	**V21**	**V22**	**V23**
Day (d)		1	2	3	4	5	8	9	10	11	12	15	16	17	18	19	22	23	24	25	26	45	90	180
Permitted delta in days (±) to d1	−42		0	0	+3	+3	+4	+4	+4	+4	+4	+4	+4	+4	+4	+4	+4	+4	+4	+4	+4	±3	±4	±5
		Treatment must be completed within 30 days, with a max. of 3 consecutive non-treatment days																						
Treatment IV 2 times daily		x	x	x	x	x	x	x	x	x	x	x	x	x	x	x	x	x	x	x	x			
Screening assessment																								
Patient information, informed consent	X																							
Inclusion/exclusion criteria	X																							
Demographics	X																							
Medical history	X																							
Diagnosis according to revised EEC	X																							
Physical examination	X																							
Randomization^#^	X^#^																							
Recurrent additional status data																								
Concomitant treatment history	X	X		X				X						X							X	X	X	X
Vital signs (pulse, BP)^**^	X	X	X	X	X	X	X	X	X	X	X	X	X	X	X	X	X	X	X	X	X	X	X	X
Height (only at screening), weight	X																				X		X	X
Endpoint assessment																								
ALSFRS-R		X																			X		X	X
Vital capacity (VC)^***^	X	X																			X		X	X
ALSAQ-5		X																			X		X	X
MUNIX		X^§^																			X		X	X
ECAS		X																			X		X	X
Safety assessment																								
Laboratory tests^^*^^,^^***^^	X	X		X				X						X							X	X	X	X
Pregnancy test^***^	X																							
Adverse events	X^****^	X	X	X	X	X	X	X	X	X	X	X	X	X	X	X	X	X	X	X	X	X	X	X

* *Laboratory tests: RBC, WBC, PLT, creatinine, GFR (MDRD), ALAT, ASAT, GGT, and CK, glucose*.

** *BP and pulse. On V1-V20 to be captured before and at 0, 10, 20, 30, 45, and 60 min after each administration of trial medication*.

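### As written, the V1 baseline serum, urine and saliva samples are drawn after the first infusion, so these three fluids have no pre-treatment value

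*Protocol article*

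**What the plan says.** The Biosample Collection Plan (protocol article) has a sampling grid, Table 3, and two timing footnotes.

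- The *** footnote is attached to the plasma row but worded for every fluid: "All biomaterials must be taken directly after administration of the trial drug in the morning except CSF". It then points to footnote X°.
- Footnote X° covers the late-treatment sample: "CSF (and concomitant plasma) analysis will be performed once 60 min after the end of trial drug infusion in the morning". In the grid, the plasma and CSF cells at V20 (exceptionally V18 or V19) carry the X° mark.

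Table 3 heads the V1 column as baseline. Study Procedures makes V1 the first treatment day: "Treatments are then performed twice daily from V1 to V20 on work days". Drug Procurement and Intervention gives the infusion time: the drug "is administered two times daily IV as infusion over 45 min".

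The V20 CSF and plasma samples "will be collected to determine the peak concentration of fasudil and hydroxyfasudil as well as ROCK activity". The same section names pharmacodynamics and disease progression among the uses of the biosamples. It adds that individual departures from the biosample plan do not count as protocol violations.

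**The concern.** A baseline for a treatment comparison should be taken before treatment. Here the column called baseline and a mandatory post-infusion rule meet on the day of the first dose. For a fluid with no earlier sample, nothing is left that treatment cannot have touched.

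If one infusion moves a marker, it does so in the two fasudil arms and not under placebo. A change from V1 would then understate the effect, and covariate adjustment for the V1 value would adjust for something measured after treatment began.

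Practice could also vary. A centre that reads the footnote literally draws after the dose, while a centre that assumes a baseline must come first draws before it. With 16 centres, and departures not classed as violations, such a mixture might not be noticed. A pre-dose sample that was not taken cannot be recovered.

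**Working it through.** No sample size, power or event figure enters this point, so there is no figure of the plan to reproduce. The check sets the grid against the treatment schedule.

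**Step 1: count pre-treatment samples under the written rule.** Sampling visits are from Table 3. Treatment visits are V1 to V20 (Study Procedures). V0 is up to 42 days before first treatment.

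| Fluid | Scheduled visits | Draws before the first infusion |
|---|---|---|
| Plasma | V0, V1, V20 (or V18/V19), V23 | 1 (V0) |
| Serum | V1, V20, V23 | 0 |
| Urine | V1, V20, V23 | 0 |
| Saliva | V1, V20, V23 | 0 |

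CSF is taken once, late in treatment, so no baseline is planned for it. Genotyping blood at V1 is not affected in substance.

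**Step 2: look for a correcting statement.** The Abstract places the baseline before therapy, but for the efficacy measures only. No section sets a pre-dose draw for serum, urine or saliva.

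**Step 3: can the rule be followed throughout?** No drug is given at V0 or V23, yet plasma is drawn at V0 and all four fluids at V23. The footnote therefore cannot apply literally at those visits, which suggests over-broad drafting.

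**Step 4: consequence for a change score.** Let *B* be the untreated level, *a* the acute effect of the first infusion on the V1 sample, and *d* the effect present in the V20 sample, all in an active arm. Leave natural progression aside, as it is common to all arms.

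- Active arm, change from V1 to V20: (*B* + *d*) − (*B* + *a*) = *d* − *a*.
- Placebo arm: *B* − *B* = 0.
- Difference in change between arms: *d* − *a*, where *d* is wanted.
- With V1 as a covariate with slope β: *d* − β*a*.
- Difference in V20 values without V1: (*B* + *d*) − *B* = *d*.

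The same holds at V23 with the effect at that visit in place of *d*. The bias is thus *a* for a change score and β*a* with covariate adjustment. The documents give no value for *a*.

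**Step 5: timing of the V20 plasma sample.** Straight after a 45-minute infusion is about 45 minutes from its start. Footnote X° gives 45 + 60 = 105 minutes. The two footnotes read separately are 60 minutes apart, but the V20 plasma cell carries X° and that footnote names the concomitant plasma.

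**The case against.** The best defence is that the article condenses a fuller protocol and that the footnote is loose drafting: it cannot apply at V0 or V23, and a pre-dose V1 draw may well have been meant. That is plausible, but the article does not say so, and the sentence is a mandatory instruction. It supports correcting the text rather than leaving it.

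Several stronger readings are tempting, and the documents do not support them.

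- *Target engagement has no pre-treatment value.* ROCK activity is listed under plasma, which is drawn at V0.
- *The change from V1 to V20 is expected to be zero however strong the drug effect.* That needs *a* = *d*, meaning the whole V20 effect is already present after one infusion. An effect that builds over 20 treatment days would still show, and nothing in the article indicates that one infusion shifts NfL, urate, p75ECR or chromogranin A.
- *Biomarker results are lost.* The trial is randomised against placebo, so V20 and V23 values can be compared between arms without V1. Secondary Outcomes lists no biomarker, and the article specifies no analysis of change from V1 for one.
- *V20 plasma has two conflicting times, with a large artefact in drug level.* The specific X° mark reasonably governs over the general row note, which itself refers to X°. What remains is a wording ambiguity, because the exception names CSF alone. Sizing an artefact would also need a half-life that the article does not give.

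One remark on the peak stands in a narrow form. Parent drug in plasma falls once a constant-rate infusion stops, so a 60-minute sample is not its peak. That does not show 60 minutes to be unsuitable for CSF or hydroxyfasudil.

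**Conclusion.** The point holds for serum, urine and saliva. Under the written rule these three fluids have 0 pre-treatment samples out of 3 scheduled draws each. Plasma has 1 out of 4 and is not affected in the same way.

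The harm is conditional. It arises if the rule is followed literally, if one infusion has an acute effect on the marker, and if V1 is used as the baseline. The bias then equals that acute effect, or β times it under covariate adjustment, and it cannot be quantified from the documents. For slowly changing markers it may be small.

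The primary endpoints, the listed secondary endpoints and the sample size are untouched. The change should be made because it is cheap and a missed pre-dose sample cannot be replaced, but the trial's main conclusions do not depend on it. The V20 plasma wording is a minor clarification only.

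**What to change.** 1. Reword the *** footnote in Table 3 so that V1 serum, urine and saliva are drawn before the first infusion, and use those values as baseline.
2. State that V0 and V23 draws are not tied to an infusion.
3. Leave V1 plasma out of this change. Its pre-dose value comes from V0, and moving the V1 draw could lose a first-dose drug level.
4. Recruitment began in 2019, so for patients already sampled record the draw time relative to the first infusion and flag post-dose baselines. Where a baseline is flagged, rely on between-arm comparison at V20 and V23 without it.
5. Minor: extend the *** exception from CSF to CSF and its concomitant plasma, so that V18–V20 plasma clearly follows the 60-minute rule. Report that plasma value as a 60-minute post-infusion level rather than as the peak of parent fasudil.

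The cost is a footnote, matching sampling instructions to the centres and one recorded time per draw. No extra samples are needed. A change during recruitment will leave a mixture of pre-dose and post-dose baselines if some were drawn as written, which is why the flag in item 4 is needed.

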### Safety

During the study, the definitions of the directive 2001/20/EC are effective. All AE, irrespective of seriousness, will be collected from the day of randomization to the follow-up visit/end of trial visit at the time points specified in the trial visits schedule. The investigator should report any AE occurring in this time period that is believed to be related to study drug or protocol-specified procedure. All SAE for which a causal relationship with the administration of study medication may not be ruled out (serious adverse reactions, SAR) need to be defined and reported as suspected unexpected serious adverse reactions (SUSAR). Once an AE is detected, it should be followed until its resolution or stabilization and assessment should be made at each visit (or more frequently, if necessary) of any changes in severity, the suspected relationship to the study, the interventions required to treat it and the outcome. All SAE will be reviewed by an independent medical monitor, who will be independent from the reporting investigator, the trial sponsor and the coordinating investigator. The investigator must carry out a causality assessment for all AEs. The relationship of an AE to the study treatment regimen has to be recorded on the CRF and defined as not related, unlikely, possible related, probable related or highly probable/definite.

Expedited reporting applies if the AE is considered serious, unexpected, and drug related (SUSAR). This type of SAE must be reported by the CRO to the appropriate national health authority and ethics committees within 15 days; fatal or life-threatening events must be reported within 7 days. All person-related data will always be transmitted pseudonymized/de-identified. The CRO will immediately, within 15 days after it becomes known, report all circumstances that require a revision of the risk-benefit analysis to the relevant ethics committees and the federal authorities. This especially includes:

Singular cases of expected SAE with an unexpected outcome.Increased incidence of expected SAE that are judged as being clinically relevant.SUSARs which occur after termination of the clinical trial (6 months) after termination or exclusion)Events related to study procedures or development of the study medication, which could affect a subject's safety.

The study will be monitored by an independent safety monitoring board (SMB), which will come together once before the start of the trial and then hold telephone conferences approximately every 3 months during the trial in order to review trial progress, safety data, and adherence to protocol, with the frequency of meetings depending on the rate of recruitment and safety issues.

### Data Recording and Study Monitoring

The documentation of the study data in adherence to the Good Clinical Practice (GCP)-guidelines and the clinical trial protocol is the responsibility of the local investigator. Original data (source documents) remain in hospital medical records and information on the eCRF must be traceable and consistent with the original data. Source documents are e.g., laboratory results, ALSFRS-R measurements, vital capacity measurements, and quality of life questionnaire. Original written informed consent signed by the patient is kept by the investigator and a signed copy will be given to the patient. No information in source documents about the identity of the patients will be disclosed. All data collected in this study must be entered in an eCRF which has to be completed by the investigator or authorized trial personnel and signed by the principle investigator. This also applies for those patients who do not complete the study. If a patient withdraws from the study, the reason must be recorded in the eCRF. The investigator is responsible for ensuring the accuracy, completeness, and timeliness of all data reported to the sponsor in the eCRFs and in all required reports.

After database lock, the principal investigator will receive data on an electronic device that includes the investigational site data for archiving in the Investigator Site File (ISF). Data are processed by data management of the CRO with the support of a study database (eCRF) according to the SOPs of the CRO. The evaluation of the data takes place by programmed validity and consistency checks.

Monitoring activities are performed to ensure that the trial is conducted in accordance with the trial protocol, the principles of GCP, and local legislation. A monitoring manual describing in detail the scope of the monitoring activities will be prepared. A monitoring visit report is prepared for each visit describing the progress of the clinical trial and all identified problems.

### Ethics and Dissemination

This trial will be conducted in accordance with the current ICH-GCP-guidelines. GCP is an international ethical and scientific quality standard for designing, conducting, recording and reporting trials that involve the participation of human subjects. Compliance with this standard provides public assurance that the rights, safety and well-being of trial subjects are protected and consistent with the principles that have their origin in the Declaration of Helsinki and that the clinical trial data are credible. Prior to study start the following documents will be obtained:

Approval of ethics committees (lead and local ethics committees)Approval of national competent authorities: Bundesamt für Arzneimittel und Medizinprodukte (BfArM), Schweizerisches Heilmittelinstitut (SwissMedic), Agence nationale de sécurité du médicament et des produits de santé (ANSM)Notification to applicable regional authoritiesInformed ConsentInsuranceData privacy and confidentiality.

Irrespective of study outcome, the results will be presented during scientific symposia and published on www.clinicaltrials.gov and in a peer-reviewed, international journal after written approval by the involved parties and respecting the privacy of the participants.

### Role of the Study Centers

In total, 16 recruiting study centers participate in the ROCK-ALS trial at the time of writing. In Germany, all centers (Berlin, Dresden, Essen, Göttingen, Halle (Saale), Hannover, Jena, Munich, Münster, Ulm, Würzburg) belong to the German Network for Motor Neuron Diseases (MND-NET) and represent specialized referral centers for motoneuron disorders. The Swiss center in St. Gallen is the largest ALS clinic in Switzerland. In France, four highly dedicated ALS referral centers participate in the trial (Marseille, Montpellier, Nice, Tours).

It is expected that each center

randomizes 8–10 patients (in France and Switzerland 6 per center), administers the treatment, performs all required clinical examinations and takes scores, collects the biospecimens, and enters all data into the eCRFcontributes at least one principle investigator, one clinical neurologist as study physician and one study nurse dedicated to the trialtrains sufficient personnel to perform MUNIX assessments.

In addition, an associated center in Warsaw (without explicit funding through E-Rare and thus outside of the formal trial protocol) will recruit patients with the same inclusion and exclusion criteria for a biosample collection, but without treatment.

Safety analyses will be performed at the local laboratories at each center. Drug levels (riluzole, fasudil, and hydroxyfasudil) will be determined at the Medizinische Labor Bremen (MLB). Multiple other research labs are foreseen for the evaluation of liquid biomarkers (e.g., neurofilament, soluble p75^ECR^, chromogranin A, and urate). In addition, we will attempt to genotype each patient by whole genome sequencing, which will be performed in collaboration with the CReATe Consortium.

The trial will be supported and monitored by the Munich Trial Center (MSZ), an academic CRO with long-standing experience in the conduct of clinical trials, particularly IITs.

### Statistical Analysis

#### Sample Size Calculation

A sample size of 102 patients (i.e., 34 patients per treatment group) yields sufficiently narrow confidence intervals for the difference in proportions between the placebo group and the treatment groups for both primary endpoints, the proportion of patients without drug-related SAEs and the proportion of patients without treatment intolerability. Under the assumption of no difference between the treatment groups and the placebo group the half-width of the 95% confidence interval for the difference in proportions is at most 0.24. Expected are high proportions of tolerability and safety in which case the confidence interval becomes narrower. If the proportion is for instance 0.9 the half-width reduces to 0.14, which is considered sufficiently narrow. Calculations were carried out using the software nQuery 4.0. Adjusting for dropout of 15% we aim to recruit a total number of 120 patients (i.e., 40 patients per treatment group).

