### Randomization, Stratification and Blinding

This trial has three parallel groups: fasudil 15 mg twice daily, fasudil 30 mg twice daily, and matching placebo. Patients are randomized to treatment using an allocation ratio of 1:1:1. The randomization list will be centrally generated using a computerized system stratified by geographical region and type of onset (bulbar, spinal). Patients will be assigned to the bulbar or spinal stratum according to the location of the earliest experienced ALS symptom (defined by the first muscle weakness or in the case of bulbar onset, by the presence of dysarthria and/or dysphagia). In the case of a patient with simultaneous onset of spinal and bulbar symptoms, onset will be defined as bulbar. Cervical and respiratory onsets are stratified to the spinal onset stratum. The randomization list will be generated by the Biometry and Bioinformatics Core using a pseudo-random number generator.

This study includes double-blind (participant- and investigator blind) treatment. Study medication will be packed and blinded by the Pharmacy at University of Leipzig Medical Center, Germany, according to the randomization list. Each patient medication package will be sent together with the sealed unblinding codes to the sites. The investigator at the site will take care that each patient is provided with the study medication box of the correct randomization number. The randomization list will be kept in safe and confidential custody at Pharmacy at University of Leipzig Medical Center, Germany. For all patients, emergency codes will be available to the investigator. A code, which reveals the treatment group for a specific study patient, may be opened during the study only if the choice of treatment depends on the study subject's therapy assignment. During the study, emergency unblinding should occur only by accessing the study patient's emergency code.

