#### Primary Analysis

The study will yield information about safety, tolerability, and efficacy. The main focus of the primary analysis is to determine whether either one or both doses are safe and tolerable. Each patient will be treated with fasudil or placebo over 45 min twice a day for 20 days. Significant drug intolerance will result in stopping the infusion and termination of the trial participation for this patient.

The proportions of patients for whom the treatment is tolerable/safe are derived for each treatment group. For both active treatment groups and for both, safety and tolerability, separately the difference in proportions to the placebo group will be calculated with its 95% confidence interval. Subsequent analyses will model tolerability and safety in logistic regressions adjusting for randomization stratification factors and important prognostic factors assessed at baseline. Treatment group differences will be reported in terms of odds ratios with 95% confidence intervals.

Primary analyses of safety and tolerability will be carried out on the ITT population. For the purpose of the tolerability analyses, subjects who discontinue during the treatment period will be considered as worst case, i.e., no drug tolerability. If a number of patients withdraw from the study following completion of the treatment period, there observations will be dealt with as independent right censoring and the time to first drug-related SAE will be considered as primary endpoint. The difference in proportions free of any drug-related SAE at V23 will be assessed using Kaplan-Meier estimates and corresponding 95% confidence intervals. Subsequent analyses will model time to first drug-related SAE in Cox proportional hazard regressions adjusting for randomization stratification factors and important prognostic factors assessed at baseline. Treatment group differences will be reported in terms of hazard ratios with 95% confidence intervals. The ITT analyses will be complemented with a per-protocol (PP) analysis. Differences between both analyses will be reported and evaluated in detail.

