#### Secondary Analysis

##### Efficacy

Efficacy outcomes including ALSFRS-R, ALSAQ-5, SVC, and MUNIX through to visit V23 will be analyzed by means of Gaussian linear model for repeated measures (so-called MMRM) with treatment group, time (visits V20, V22, V23), treatment-by-time interaction, region, and stratum of onset as factors and baseline measurements of the outcome as covariate. The error terms are assumed to follow a multivariate normal distribution with unstructured covariance. Least squares mean changes from baseline will be reported for the treatment groups with 95% confidence interval (CI) as well as the difference between the least squares treatment group means with 95% CI and *p*-value testing the null hypothesis of no treatment effect. The analysis will be primarily performed on the ITT population, but complemented by PP analysis.

Survival time will be used as a secondary endpoint. The Kaplan-Meier method will be applied to estimate the survival probabilities in each group. The 95% CIs will be calculated with the variance derived according to Greenwoods' formula. Subjects will be right-censored at end of their follow-up. Pairwise group comparisons against placebo will be analyzed using exact log rank tests. Cox proportional hazards regression will be carried out if there are a sufficient number of events.

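### Precision is planned with the Wald formula, the primary interval method is unnamed, and the adjusted models of the primary endpoints carry no event condition although few events may occur

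*Protocol article*

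**What the plan says.** Under Sample Size Calculation, the protocol article bases the trial size on interval width: "A sample size of 102 patients (i.e., 34 patients per treatment group) yields sufficiently narrow confidence intervals". Assuming no difference between arms, "the half-width of the 95% confidence interval for the difference in proportions is at most 0.24". It continues: "Expected are high proportions of tolerability and safety in which case the confidence interval becomes narrower", and then: "If the proportion is for instance 0.9 the half-width reduces to 0.14, which is considered sufficiently narrow". A dropout allowance of 15% raises the total to 120, or 40 per arm.

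Under Primary Analysis, each active arm is compared with placebo by a difference in proportions with a 95% interval, for safety and for tolerability. No interval method is named. If patients withdraw after the treatment period, the safety comparison changes form: "The difference in proportions free of any drug-related SAE at V23 will be assessed using Kaplan-Meier estimates and corresponding 95% confidence intervals". No variance or transformation is named there either. Supporting models follow: "Subsequent analyses will model tolerability and safety in logistic regressions adjusting for randomization stratification factors and important prognostic factors assessed at baseline". In the withdrawal case a Cox model for time to first drug-related SAE, with the same adjustment, is added. Neither model depends on the number of events.

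Under Efficacy, for survival time only, the article does name a variance: "The 95% CIs will be calculated with the variance derived according to Greenwoods' formula". There, Cox regression is to be run only if there are enough events.

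**The concern.** The main product of this phase IIa trial is a set of intervals for the excess of drug-related SAEs and of intolerance over placebo. The plan expects proportions close to 1, which is where the planning formula is weakest. Wald variance is zero in an arm without events, so the interval can suggest far more certainty than 34 or 40 patients can give. The case that matters is a true difference near the boundary, because that is what drug harm would look like, and there a Wald interval can understate the excess risk still compatible with the data.

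The models raise a second problem that does not depend on the interval method. If placebo or the compared active arm has no event, the maximum-likelihood log odds ratio or log hazard ratio diverges, and the promised ratio with its 95% interval cannot be reported in the usual way. The article guards against sparse events for a secondary endpoint but not for the primary ones.

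**Working it through.** **Inputs from the article:** 34 evaluable and 40 recruited patients per arm, equal allocation, 95% intervals, half-widths 0.24 and 0.14, example proportion 0.9, dropout 15%. **Assumed:** proportions above 0.9. The article says only that they are high, so a range is shown. An event is a drug-related SAE or an intolerance.

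**1. The plan's own figures.** Wald half-width = 1.96 × √(2p(1−p)/n), with n = 34:
- p = 0.5: 1.96 × √(0.50/34) = 0.238, stated as 0.24
- p = 0.9: 1.96 × √(0.18/34) = 0.143, stated as 0.14

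A continuity correction would give 0.267 and 0.172, which do not match. Recruitment: 102/0.85 = 120, as stated.

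**2. Score-type half-widths (Newcombe).**
- 31/34 v 31/34: 0.153 (Miettinen-Nurminen 0.157). The expected value at p = 0.9 is 0.156.
- 36/40 v 36/40: 0.144
- No events in either arm: 0.102 with 34 per arm and 0.088 with 40. Wald gives 0 in both cases.
- Expected at p = 0.95: 0.132 with 34 per arm and 0.119 with 40

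The score interval also narrows as p rises, but less, and it does not go to zero.

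**3. Wald coverage by exact binomial enumeration.**

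| True proportions | n = 34 | n = 40 |
|---|---|---|
| 0.90 v 0.90 | 94.1% | 94.1% |
| 0.95 v 0.95 | 96.5% | 95.7% |
| 0.98 v 0.98 | 99.5% | 99.3% |
| 0.90 v 0.95 | 94.7% | 93.9% |
| 0.95 v 0.98 | 82.2% | 86.3% |
| 0.97 v 0.99 | 74.4% | 78.0% |

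Newcombe covers at least 96% in each of these rows. As an example of the consequence, take 2 failures of 40 on active treatment and 0 of 40 on placebo: the lower limit for the difference is −0.118 with Wald and −0.165 with Newcombe.

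**4. Collapse to [0, 0].** The probability is p^(2n) when both arms share p. With 40 per arm it is p^80: below 0.1% at 0.90, 2% at 0.95, 9% at 0.97, 20% at 0.98 and 45% at 0.99.

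**5. Events for the models.** Expected events = 120 × (1−p). The probability that placebo or the compared active arm has none is 1 − (1 − p^40)².

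| p | Expected events of 120 | P(no event in at least one of the two arms) |
|---|---|---|
| 0.90 | 12 | 2.9% |
| 0.95 | 6 | 24% |
| 0.97 | 3.6 | 50% |
| 0.98 | 2.4 | 69% |

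The models need two treatment terms, one onset term and at least one region term (assuming two or more regions), so at least four parameters before any prognostic factor. That is at most 12/4 = 3 expected events per parameter at 0.90 and 6/4 = 1.5 at 0.95.

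**The case against.** Planning with a normal approximation and analysing with a score interval is ordinary practice, and the interval method may well be fixed in an analysis plan that is not at hand. A reader might infer that the primary intervals are Wald or Greenwood intervals. The article does not say so: it names no method for the primary comparison, and it ties Greenwood's formula to secondary survival only. The fault is therefore conditional on the planning formula being carried over.

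A reader might also infer that the interval fails where the sponsor expects to land. At 0.9, the only proportion given, Wald covers 94.1% and collapse is negligible. Under the planning assumption of no difference it does not undercover near 1 either, because the collapsed interval contains the true difference of 0. The sentence about narrowing is true of score intervals too, and the gap between 0.14 and 0.15–0.16 is small. With 40 per arm the score figure is itself about 0.14.

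Tolerability is less exposed, because every discontinuation during treatment counts as intolerance. At 0.85, for example, the chance of an event-free arm in a comparison is 0.3% with 40 per arm. Finally, the models are supporting analyses, and the Cox model arises only in the withdrawal case.

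All of this stands and limits the point. It does not remove the unconditional modelling commitment, which is in the text and differs from the rule set for survival.

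**Conclusion.** The point holds in two limited parts. First, the precision figures are Wald figures and somewhat optimistic near 1. If the same method is used in the analysis, it can return a zero-width interval, and its coverage falls to 86% (0.95 v 0.98) or 78% (0.97 v 0.99) with 40 per arm. This needs proportions near 1 that differ between arms, which is an assumption and fits rare drug-related SAEs better than tolerability.

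Second, the adjusted logistic and Cox models of the primary endpoints have no event condition. If the true proportion is 0.95 or higher in all arms, at least about one pairwise comparison in four would have no finite estimate; at 0.90 it is about 3%. The sample size and the design are not in question.

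**What to change.** In Primary Analysis, or in the analysis plan:
- Name a score-type interval (Miettinen-Nurminen or Newcombe) for each difference in proportions.
- For the Kaplan-Meier difference, name an interval that respects the boundary, for example one combining per-arm Wilson limits on the effective sample size.
- Fit the logistic and Cox models with Firth's penalty, or use an exact method, with covariates limited to treatment and the randomisation factors. Alternatively, apply the event condition already used for survival.

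Optionally, add to Sample Size Calculation that the score half-width at 0.9 is about 0.15–0.16 with 34 per arm (about 0.14 with 40), and that with no events it does not fall below about 0.10 (0.09 with 40).

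The cost is wording and standard software. Intervals become slightly wider, odds and hazard ratios are shrunken, and fewer prognostic factors are adjusted for. The sample size stays at 120.
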